## Abstract

**Introduction:**

Spinal cord injury (SCI) at or above the thoracic sixth spinal cord level disrupts descending sympathetic and parasympathetic control, leading to severe autonomic dysfunctions including cardiovascular and pelvic organ function. These complications adversely affect the quality of life and are associated with increased morbidity and mortality after SCI. Transcutaneous spinal cord stimulation (tSCS) may offer therapeutic benefits for these functions. The safety of tSCS in subacute SCI, however, remains unknown. Therefore, this study aims to evaluate the feasibility of tSCS for autonomic recovery in individuals with subacute SCI within six months since injury.

**Methods and analysis:**

We designed a two-phase clinical protocol consisting of a pilot randomized controlled trial conducted during inpatient rehabilitation (Project A), followed by a post-discharge outpatient phase with a single-arm quasi-experimental design (Project B). In Project A, 26 adults with cervical or upper thoracic (≥T6) American Spinal Injury Association Impairment Scale (AIS) A-C SCI are planned to be enrolled and randomly assigned to receive tSCS or sham stimulation for five sessions (up to 90 minutes each) in parallel with standard care. Following discharge from inpatient rehabilitation, eligible participants will be offered continuation in Project B. New eligible participants who have not participated in Project A will also be recruited into Project B. They will receive 18 tSCS sessions over six weeks in the laboratory setting. Primary outcomes focus on feasibility, including recruitment, retention, and stimulation-related adverse events. Clinical outcomes will be collected at baseline, after each intervention, and at six months and one-year post-injury. Feasibility results will be summarized descriptively, and exploratory analyses of autonomic outcomes, including cardiovascular and pelvic organ function, will provide preliminary estimates of autonomic responses.

**Ethics and dissemination:**

The study has been approved by the University of Washington Institutional Review Board. Written informed consent will be obtained from all participants. Results will be submitted to peer-reviewed journals and shared with the scientific/clinical communities and individuals with lived experience of SCI.

**Trial registration:**

ClinicalTrials.gov NCT06540859

## Background

Recent global estimates indicate that approximately one million new spinal cord injuries (SCI) occur each year, and more than 20 million individuals are living with SCI [1]. While paralysis is widely recognized as the most apparent and debilitating consequence of SCI, cardiovascular dysfunction is consistently reported as a leading health concern and the primary cause of mortality in this population [2–5]. Injuries at or above the level of sixth thoracic spinal cord segment (≥T6) disrupt descending supraspinal sympathetic control [6]. Loss of sympathetic outflow compromises vascular tone, which is essential for maintaining of arterial blood pressure [7].

Following SCI, the autonomic nervous system enters a state of neurogenic shock due to the loss of descending tonic sympathetic control and the dominance of parasympathetic activity [8]. Neurogenic shock typically lasts days to weeks following the injury onset [9]. During neurogenic shock, individuals with SCI experience profound hypotension and bradycardia, often requiring vasopressor support [10]. Although neurogenic shock itself eventually resolves, cardiovascular instability frequently persists beyond the acute phase because of loss of supraspinal regulation of autonomic spinal cord circuits below the lesion [11]. This impaired control manifests by variety of cardiovascular dysfunction including orthostatic hypotension, characterized by blood pressure (BP) reductions during postural changes [12], and autonomic dysreflexia, marked by excessive hypertension in response to visceral stimuli such as bladder and bowel distension [13]. Both orthostatic hypotension and autonomic dysreflexia can cause rapid and severe BP changes that are life-threatening [14].

SCI disrupts the crucial communication between spinal autonomic circuits and supraspinal control centers, resulting not only in impaired cardiovascular control but also in gastrointestinal and genitourinary system dysfunction [15]. These autonomic impairments are among the most important determinants of dignity, autonomy, and health [16,17]. Neurogenic bowel dysfunction results from impaired complex autonomic and somatic systems following SCI, and cardiovascular dysregulation during bowel management can induce clinically serious hypertensive episodes of autonomic dysreflexia, particularly in individuals with cervical and high thoracic SCI [18,19]. Therefore, there is a critical and urgent need for therapeutic approaches that extend beyond cardiovascular control and address multiple autonomic domains, including bowel and bladder function.

Engaging in targeted therapies during the acute and subacute phase, the critical window, may promote autonomic recovery [12,20]. Although sensorimotor function has been studied in the acute phase [21], only a few studies have focused on autonomic recovery. Evidence suggests that maintaining an optimal BP range during the acute phase promotes spinal cord recovery [22], and mean arterial BP management with vasopressor within one week of onset improves long-term neurological outcomes [23]. Pharmacological agents such as midodrine improve orthostatic tolerance in the acute phase [24,25]. Although midodrine may be effective for some individuals with SCI, its widespread use for treating orthostatic hypotension and orthostatic intolerance in this population remains questionable [26], and it may also exacerbate autonomic dysreflexia [27,28]. Prazosin can reduce autonomic dysreflexia severity but may induce a ‘first-dose phenomenon.’ Given the transient and fluctuating nature of BP in SCI, long-acting agents such as midodrine and Prazosin may not be ideal [12,29]. While topical nitropaste is also effective for acute management of autonomic dysreflexia, it has important limitations, including the risk of potential exacerbation of orthostatic hypotension and contraindications with phosphodiesterase-5 inhibitors [30]. In addition, non-pharmacological approaches such as verticalization in intensive care units have also shown long-term benefits [31]. However, the efficacy of interventions remains limited [32], and current clinical options are insufficient [12,29]. Therefore, there is an unmet need for novel therapeutic approaches that can prevent and target multiple dysfunctions while minimizing adverse effects.

Recent studies demonstrate that invasive epidural spinal cord stimulation (eSCS) can enhance autonomic function after cervical and upper thoracic SCI [33–36]. In acute and subacute SCI, animal studies in rodents and non-human primates demonstrate that eSCS can restore and maintain hemodynamic stability within hours after SCI [37]. Despite these benefits, the requirement for surgery and the associated costs restrict its broader application. In contrast, transcutaneous spinal cord stimulation (tSCS) offers a practical alternative that is non-invasive, less expensive, and allows electrode repositioning to target multiple spinal regions. Evidence suggests that tSCS engages spinal neural pathways in a manner similar to eSCS [38–40]. The real-time application of tSCS can potentially improve BP control and mitigate the episodes of autonomic dysreflexia in response to digital anorectal stimulation without delayed onset in individuals with chronic SCI [41,42]. Long-term application of tSCS has been shown to produce neurological and motor improvements that persist in the absence of stimulation in multicenter clinical trials [43].

In parallel, growing evidence suggests that recurrent tSCS may modulate autonomic cardiovascular regulation and neurogenic bowel dysfunction in chronic SCI with the absence of significant cardiovascular adverse events [44–46]. Clinical trials conducted in inpatient rehabilitation settings have demonstrated significant improvements in motor function, walking function, and functional independence at short-term follow-up [47]. Additionally, a recent study conducted in an inpatient rehabilitation setting examined the safety and feasibility of single-session, real-time tSCS for immediate blood pressure control in individuals with SCI [48]. However, there are no studies that have yet tested the effect of recurrent tSCS on comprehensive cardiovascular function including orthostatic hypotension and autonomic dysreflexia as well as pelvic organ function in subacute SCI, up to six-month post-injury. Thus, we aim to investigate the safety and feasibility of tSCS following acute SCI to treat a comprehensive range of autonomic dysfunctions.

Studying neuromodulation–based interventions in subacute SCI presents substantial ethical, logistical, and methodological challenges. Thus, transparent protocol-level reporting is therefore essential to ensure methodological rigor, mitigate selective reporting and publication bias, and enhance the interpretability and reproducibility of findings [49–51]. Publishing this protocol separately provides a pre-specified and transparent account of the study design, helping to mitigate selective outcome reporting and undisclosed analytical flexibility [52–54], while supporting scientific rigor and reproducibility through detailed documentation of stimulation parameters, titration procedures, and implementation strategies [55,56]. In accordance with the Standard Protocol Items: Recommendations for Interventional Trials (SPIRIT) guidelines, this protocol aims to provide a standardized and reproducible framework that may inform future trials incorporating rigorous randomized designs, appropriate sham controls, and standardized outcome measures, as well as clinical implementation of tSCS for autonomic recovery after SCI [57,58].

### Trial objectives

We hypothesize that tSCS can be safely administered during subacute SCI and will result in superior recovery of cardiovascular and pelvic organ functions. Our study is formed of the following aims: to assess the feasibility of single tSCS sessions in subacute SCI (Aim 1), to assess the feasibility of recurrent tSCS on autonomic function in subacute SCI (Aim 2), and to evaluate the preliminary effects of recurrent tSCS on autonomic recovery (Aim 3). These trial objectives and following study design are constructed based on the CONSORT statement and extension to pilot trials.

## Methods and analysis

### Study design and setting

The trial timeline, flow and experimental design is illustrated in Figs 1 and 2. We designed a two-phase clinical protocol consisting of a pilot randomized controlled trial (RCT) (Project A, Fig 2) followed by an outpatient continuation phase (Project B) designed as a within-subject, longitudinal feasibility study. Changes across a comprehensive range of autonomic dysfunctions are examined over repeated sessions, without a parallel control group, to reduce participant burden and allow inclusion of individuals transitioning from inpatient rehabilitation.

**Fig 1 pone.0347211.g001:**
[figure not shown]
The standard protocol items: recommendations for interventional trials (SPIRIT) schedule: Enrollment, interventions, and assessments. V = Visit. tSCS = transcuntaneous spinal cord stimulation. ECG = Electrocardiography. BP = Blood pressure. SCI = Spinal cord injury.

**Fig 2 pone.0347211.g002:**
[figure not shown]
Trial flow and design of Project A. SCI = spinal cord injury. IRF = inpatient rehabilitation facilities. tSCS = transcuntaneous spinal cord stimulation.

In Project A, we propose a pilot RCT with blinding subject and assessor, two-arm sham-control to evaluate the safety and efficacy of tSCS over the lower thoracic and upper lumbar spinal cord segments for cardiovascular function in adults (18–65 years old) with cervical and upper thoracic SCI (≥T6) American Spinal Injury Association Impairment Scale (AIS) A-C during subacute inpatient rehabilitation. We will recruit 26 individuals with SCI, admitted to inpatient rehabilitation facilities (IRF) (average 8–10 days post-injury). We will conduct this study in the University of Washington Harborview Medical Center (HMC).

Eligible participants will be randomly assigned into two groups as follows: One arm will receive sham stimulation for 30–60 minutes for a total of five sessions, during their IRF stay while maintaining intensive rehabilitation (Sham Group, n = 13). A second arm will receive tSCS for 30–60 minutes for a total of five sessions, in IRFs while maintaining intensive rehabilitation (tSCS Group, n = 13). The intervention frequency and duration are constrained due to the inpatient schedule. We will apply tSCS at rest while maintaining conventional physical therapy, occupational therapy and speech therapy to control for the combinatory effect. This study design also controls for the placebo effect by blinding participants, healthcare professionals, and assessors but not researchers who deliver the intervention. We will collect all outcomes over six months, with three assessments, one at each timepoint of IRF admission, post-interventions, and six-month follow-up.

Following discharge, participants who remain eligible and are able to commute will be offered enrolment in Project B. In addition, new eligible participants, who did not participate in Project A and are less than four months since the injury onset, will be screened and recruited into Project B. All participants who remain eligible from Project A, including those who received sham stimulation during Project A, will be eligible to participate. This project will utilize a single-arm quasi-experimental design in the laboratory setting. Participants will receive a total of 18 sessions of active tSCS for 60–90 minutes over six weeks to assess feasibility and longer-term autonomic adaptations. tSCS will be delivered at rest, separate from scheduled physical or occupational therapy sessions. All outcomes will be collected up to six months post-injury, with assessments conducted at three time points: baseline, after completion of the 18-session outpatient phase (Project B), and at six months follow-up. Participant recruitment for this study began on December 1, 2024, and is expected to be completed by September 30, 2026, with data collection for all study phases including six months follow-up anticipated to conclude by April 30, 2027. Final analyses and dissemination of the study results are expected by July 30, 2027. Written informed consent is obtained from all participants prior to enrolment. This study was approved by the University of Washington Institutional Review Board on May 6, 2024. This trial was registered at ClinicalTrials.gov (NCT06540859). The authors confirm that all ongoing and related trials for this intervention are registered.

### Sample size

We aim to recruit 26 participants with SCI for Project A admitted to IRF (average 8–10 days post-injury). Project B will include participants continuing from Project A as well as additional eligible participants recruited post-discharge. A sample size calculation was performed using G*power software [59] with power set at 0.80 and α at 0.05. We conducted the power analysis based on one SCS study for BP control assessed by head-up tilt test with and without eSCS (n = 4, cervical motor-complete AIS A or B) [33]. A minimum sample of 11 participants is required to detect a significant change in systolic BP during head-up tilt test (mean systolic BP change between stim-off and stim-on = 16.2 ± 12.6 mmHg, effect size = 1.29). Considering a potential 20% dropout rate [60], we aim to recruit 13 individuals with SCI to each group, for a total of 26 individuals with SCI.

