### Statistical analysis

This is a two-phase clinical trial consisting of a pilot RCT (Project A) followed by a single arm pre- and post-experimental trial (Project B). A total of 26 participants with subacute (<six months since injury) cervical or upper thoracic ≥T6 AIS A–C SCI will be enrolled (Sham group n = 13, tSCS group n = 13). Descriptive statistics will be generated for the primary outcomes, feasibility outcomes, as well as demographic a clinical characteristic. Between group comparisons at baseline will be conducted using independent sample t-tests, Chi-square analyses, and Mann Whitney U tests as appropriate. Statistical analysis will be performed using R version 4.1.2 and the R studio program. This study is designed as a pilot trial, and analyses will primarily focus on feasibility, safety, and exploratory trends. Results will be interpreted in accordance with the CONSORT extension for pilot and feasibility trials

For Aim 1, we will evaluate the feasibility of tSCS by comparing cardiovascular responses before, during and after single and repeated tSCS sessions. Changes in systolic and diastolic BP and heart rate will be analysed using linear mixed models for repeated measures, with time (session) as a within-subject factor. Additionally, feasibility outcomes, including adherence rate, recruitment rate, and the frequency of adverse events, will be summarized descriptively.

For Aim 2, we will use Between-participant analyses assessing group differences in feasibility and preliminary autonomic outcomes between the Sham and tSCS groups after completion of the five-session inpatient phase (Project A). Linear mixed models will be used to assess the effects of time and intervention group, with baseline values included as covariates.

For Aim 3, within-participant analyses will examine longitudinal changes following the 18-session outpatient continuation phase (Project B) and at six-month follow-up. Descriptive statistics and standardized effect sizes (Cohen’s d) will be reported to estimate the magnitude of changes.

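### The stated 80% power is unsupported for sham versus tSCS because it borrows a within-person epidural effect from 4 people, and 13 per arm covers about 15% dropout, not 20%

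*Protocol article*

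**What the plan says.** All the inputs are in the Protocol article, Sample size section.

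- Error rates: "with power set at 0.80 and α at 0.05". Neither the test nor its sidedness is named.
- Source of the effect: "one SCS study for BP control assessed by head-up tilt test with and without eSCS (n = 4, cervical motor-complete AIS A or B".
- Effect: "mean systolic BP change between stim-off and stim-on = 16.2 ± 12.6 mmHg, effect size = 1.29".
- Required number: "A minimum sample of 11 participants is required to detect a significant change in systolic BP during head-up tilt test". It is not labelled as per group or in total.
- Recruitment: "Considering a potential 20% dropout rate [60], we aim to recruit 13 individuals with SCI to each group, for a total of 26 individuals".

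The Statistical analysis section plans a baseline-adjusted linear mixed model of sham versus tSCS for Aim 2, after the five inpatient sessions. For Aim 3 it plans within-participant descriptive analyses. It also says that "analyses will primarily focus on feasibility, safety, and exploratory trends".

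**The concern.** There are two separate problems in one paragraph.

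**The effect and the comparison do not match.** The 1.29 is a mean within-person change divided by the SD of that change. It was measured acutely, with epidural stimulation switched off and on in the same 4 people. The calculation then sizes two parallel arms that receive sham or transcutaneous stimulation over five sessions. Carrying the figure across needs an expected sham response and an SD for the between-arm comparison. The protocol gives neither.

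**The dropout allowance does not do what it says.** The number recruited per arm, less the stated dropout, falls short of the stated minimum.

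What is at stake is how Project A is read. With a stated power of 0.80 on record, a non-significant sham-versus-tSCS difference in systolic BP could be taken as reasonable evidence of no effect, which this calculation cannot support.

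**Working it through.** **Inputs (Protocol article, Sample size):** mean change 16.2 mmHg, SD 12.6 mmHg, source n = 4, power 0.80, α 0.05, stated n 11, dropout 20%, 13 per arm. Power below comes from the noncentral t distribution.

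**1. Reproduce the plan's figure.** d = 16.2/12.6 = 1.286, stated as 1.29.

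| Calculation at d = 1.29 | n needed for 80% power |
|---|---|
| Independent groups, two-sided t | **11 per group** (power 0.821; 10 per group gives 0.779) |
| Independent groups, one-sided t | 9 per group |
| Independent groups, normal approximation | 10 per group two-sided; 8 one-sided |
| Paired, two-sided t | 7 in total (power 0.810) |
| Paired, one-sided t | 6 in total |

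Only the first row gives 11. Read instead as 11 people in total, split 5 and 6, the two-sided two-group power would be 0.48. So 11 has to mean per group, which agrees with the later allocation of 13 to each arm. The test is inferred from this match, because the text does not name it.

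**2. Dropout.**

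- Needed per arm: 11/(1 − 0.20) = 13.75, so 14 per arm (28 in total).
- Left from 13 per arm: 13 × 0.8 = 10.4, below 11.
- Dropout that 13 can absorb: 1 − 11/13 = 15.4%.
- The stated 13 equals 11 × 1.2 = 13.2 rounded down, which may be how it arose.
- If each participant drops out independently with probability 0.20, both arms keep at least 11 with probability about 0.25.

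Power at d = 1.29, two-sided:

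| Completers | Power |
|---|---|
| 13 + 13 | 0.884 |
| 11 + 11 | 0.821 |
| 10 + 11 | 0.800 |
| 10 + 10 | 0.779 |
| Averaged over binomial 20% loss from 13 + 13 | 0.788 |

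The slip therefore costs about 2 percentage points at most against the stated 0.80.

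**3. What the borrowed effect implies for sham versus tSCS.** The protocol gives no between-person SD, no off/on correlation ρ and no sham response, so no single corrected n can be computed. The values of ρ below are assumptions.

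*(a) Arms compared on raw systolic BP, zero sham change.* SD = 12.6/√(2(1 − ρ)) and d = 16.2/SD.

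| ρ | SD (mmHg) | d | n per arm for 80% | Power at 10 per arm |
|---|---|---|---|---|
| 0.3 | 10.6 | 1.52 | 8 | 0.90 |
| 0.5 | 12.6 | 1.29 | 11 | 0.78 |
| 0.7 | 16.3 | 1.00 | 17 | 0.56 |
| 0.8 | 19.9 | 0.81 | 25 | 0.41 |
| 0.9 | 28.2 | 0.57 | 49 | 0.23 |

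*(b) 12.6 taken as the SD of change in each arm, zero sham change, baseline-adjusted.* d = 1.29/√((1 + ρ)/2). At ρ = 0.3, d = 1.60 and power at 10 per arm is 0.92. At ρ = 0.9, d = 1.32 and power is 0.80.

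Across these readings, power with 10 completers per arm runs from 0.23 to 0.92.

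**4. Precision of the source.** SE = 12.6/√4 = 6.3, t(0.975, 3 df) = 3.182, half-width 20.0. The 95% CI for the mean change is about −3.8 to 36.2 mmHg, and for the standardized effect about −0.14 to 2.63.

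**5. Detectable difference.** The standardized difference giving 80% power, two-sided, is 1.32 with 10 per arm, 1.26 with 11 and 1.15 with 13.

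**The case against.** The strongest defence has four parts.

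- **The SD of a change is a legitimate input for comparing changes between two arms.** If sham change is zero and 12.6 mmHg applies in both arms, 1.29 is coherent, and the planned baseline adjustment could raise power. This stands. It means that using 1.29 in a two-group test is not in itself an error of formula. The assumptions that make it coherent are still unstated, and nothing in the protocol supports carrying an acute epidural contrast over to five transcutaneous sessions.
- **The off/on contrast is measured.** The Assessments section has all participants do a sit-up or tilt test with and without tSCS. A paired test at 1.29 has power 0.95 with 10 people and 0.99 with 13. This also stands, so it would be wrong to say that the trial never observes the contrast. But that contrast needs 7 people in total, so it does not explain 11 per group.
- **The trial is a pilot.** Feasibility leads Aim 2, between-group differences are exploratory, and the source's n = 4 is disclosed. This limits the consequence. It does not correct the figures.
- **The dropout slip is small.** It is, as shown above.

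A reader might go further and infer that the design lacks 80% power, or that true power is well under 60%. The documents do not support that. On the plan's own inputs, power after 20% loss is about 0.78–0.80. Much lower figures need assumed correlations, SDs or smaller effects, and other equally open assumptions give 0.90 or more.

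**Conclusion.** The point holds in two parts, and its severity is minor to moderate.

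1. **Power is unsupported, not disproved.** The 0.80 applies to sham versus tSCS only if sham change is zero and the SD of 12.6 mmHg from 4 people with epidural stimulation carries over. The protocol supports neither condition. This rests on inferring the two-sided independent-groups t-test, the only calculation tried that returns 11.
2. **The dropout figure is wrong on the plan's own numbers.** Thirteen per arm leaves 10.4 at 20% loss. Fourteen per arm would be needed, or the tolerated dropout is about 15%. No outside assumption is involved, and the effect on power is at most about 2 points.

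Neither part calls for a different trial size. The practical risk is over-reading a null exploratory between-group result.

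**What to change.** Revise the Sample size paragraph and keep 26 participants:

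- Write 11 **per group**, and name the test and its sidedness (a two-sided independent-groups t-test, if that is what was run).
- State either that 13 per arm retains 11 up to about 15% dropout, or that power at 20% dropout is about 0.78–0.80 at an effect size of 1.29.
- State that the effect is borrowed from an acute within-person epidural contrast in 4 people, and that zero sham change and an equal SD are assumed.
- State that, with 10–11 completers per arm, 80% power for sham versus tSCS holds only for standardized differences of about 1.3 or more (1.32 to 1.26), so a null exploratory between-group result is not evidence of no effect.

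As an optional addition, 26 can be justified by feasibility precision. For example, retention of 21/26 (81%) has an exact 95% CI of 61–93%, and zero events in 13 active participants excludes a rate above 1 − 0.05^(1/13) = 21% (one-sided 95%).

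The cost is the wording of one paragraph and a less favourable stated figure. No participants or procedures are added, and the analysis does not change.
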